
Our primary aims are:

1. To determine whether vitamin D supplementation in the pregnant mother is associated with reduced incidence of asthma in the child during the first 3 years of life. Our primary outcomes will be doctor's diagnosis of asthma and/or recurrent wheeze in the child at age 3 years.

2. To determine whether a vitamin D dose of 4,400 IU per day vs. the standard 400 IU/day in pregnancy is sufficient to maintain mothers' vitamin D levels in the range of  $\geq 75$  nmol/L 25(OH)D.

In addition to our primary aims, we have the following secondary aims of the trial:

3. To determine whether vitamin D supplementation in the pregnant mother is associated with reduced secondary outcomes in the neonate of cord blood total IgE, and reduced secondary outcomes in the 3-yr old child of (a) allergic sensitization (total and specific IgE), (b) eosinophil count, (c) doctor's diagnosis of eczema and (d) lower respiratory tract infections.
4. To determine whether vitamin D supplementation in the pregnant mother is associated with improved vitamin D status in their offspring through measurement of 25(OH)D levels in cord blood (at delivery), and children's blood (at 1 and 3 yrs of age).
5. To determine whether sufficient vitamin D supplementation in the pregnant mother is associated with reduced incidence of preterm birth (birth <37 weeks gestation), preeclampsia, gestational hypertension, and/or Hemolytic anemia, Elevated Liver enzymes, Low Platelet count (HELLP syndrome) (PB/PE) compared to a usual care control group in VDAART.

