#### **P.2.a. Plan for *Specific Aim 1***

The hypothesis that the incidence of asthma and recurrent wheeze at age three years is reduced in the high-dose Vitamin D supplementation group will be tested using logistic regression, allowing for fixed effects of center. Additional analyses will consider the modification of vitamin D exposure effects by maternal and child demographic/behavioral factors such as maternal age, BMI and weight gain during pregnancy, maternal history of asthma/allergy, and other factors potentially associated with asthma and/or vitamin D exposure. The variables to be considered are summarized in Table 3. For variables that are measured post-natally, recall bias is a potential confounder among parents of infants diagnosed with asthma. However, the prospective nature of the data collection should limit the extent of this and other potential sources of bias. Due to the design of this clinical trial, we expect that the randomization process will distribute these variables equally between the intervention and control groups. However, we will check the distribution of these variables prior to conducting the analyses, and will adjust for variables that may be unevenly distributed across treatment and control groups.

**Table 3. Information on selected potential confounders of the relationship between 25(OH)D levels and asthma/recurrent wheeze in 3-yr old children**

|                                  |                                                                                 |
|----------------------------------|---------------------------------------------------------------------------------|
| Prenatal variables               | Socioeconomic status                                                            |
|                                  | Maternal diet                                                                   |
|                                  | Maternal sun exposure behavior                                                  |
|                                  | Maternal age and parity                                                         |
|                                  | Maternal history of asthma and allergies                                        |
|                                  | Maternal pre-pregnancy BMI and weight gain in pregnancy                         |
|                                  | Maternal medication use in pregnancy (antibiotics, acetaminophen, NSAIDs, etc.) |

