|                                  | Pregnancy complications (e.g. gestational diabetes, pre-eclampsia)              |
|                                  | Maternal depression                                                             |
|                                  | Maternal stress                                                                 |
| Delivery variables               | Gestational age                                                                 |
|                                  | Mode of delivery (caesarian section, normal vaginal delivery)                   |
|                                  | Birthweight, length, head circumference                                         |
|                                  | Oxygen use                                                                      |
|                                  | Need for NICU stay                                                              |
| Postpartum and infancy variables | Breastfeeding or bottle feeding                                                 |
|                                  | Type of formula                                                                 |
|                                  | Timing and type of solid food introduction                                      |
|                                  | Daycare, including timing of and type of daycare (home vs. institution)         |
|                                  | Pets in the home                                                                |
|                                  | Other siblings in the home (gender and number)                                  |
|                                  | Smoking in the home                                                             |
|                                  | Childhood diet                                                                  |
|                                  | Sun exposure behaviors in the child                                             |
|                                  | Maternal depression                                                             |
|                                  | Maternal stress                                                                 |

Letting  $M_i$  be an indicator function for the primary endpoint, asthma, for the  $i^{\text{th}}$  subject, the model is:

$$\text{logit Pr}(M_i = 1 \mid x_i, a_i) = \alpha + \beta x_i + \gamma_1 a_{1,i} + \gamma_2 a_{2,i}$$

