where  $x_i$  denotes an indicator function for level of vitamin D supplementation (0=400 IU, 1=4400 IU) in the  $i^{\text{th}}$  subject, while  $a_{1,i}$  and  $a_{2,i}$  are indicator functions for study center. The specific aim for this outcome tests the hypothesis that  $\beta=0$ , asthma and recurrent wheeze incidence do not significantly differ across treatment groups, after adjusting for the potential effects of study center heterogeneity.

To assess modification of vitamin D exposure levels by other demographic and/or behavioral variables, the model is:

$$\text{logit Pr}(M_i = 1 \mid x_i, a_i) = \alpha + \beta x_i + \gamma_1 a_{1,i} + \gamma_2 a_{2,i} + \sum_k \delta_k z_{ki} + \sum_k \eta_k x_i z_{ki}$$

where  $z_{ki}$  represents the  $k$  measured covariates for each subject, and the other variables are as described above. This model addresses two hypotheses. First, main effects testing for behavioral/demographic covariates (Table 3), or the hypothesis that  $\delta_k=0$ , will be used to examine whether maternal age, BMI, or other factors predict asthma and recurrent wheeze risk at age 3. More importantly, inclusion of any significant main effects will adjust for any distributional imbalances of these factors across the Vitamin D supplemented and placebo

groups. Second, this model tests the hypothesis that  $\eta_k=0$ , or whether any maternal, child, or demographic/behavioral covariates modify the relationship between vitamin D intake and our primary outcome. To obtain a parsimonious model and limit multiple testing, only covariates with significant main effects and strong biologic plausibility for an exposure-dependent impact on asthma/recurrent wheeze risk will be considered for interaction testing with Vitamin D supplementation status. For example, only the prenatal and some delivery variables (e.g., gestational age, birthweight, length) listed in Table 3 will be considered, as the factors modifying the impact of Vitamin D supplementation on asthma and/or recurrent wheeze should occur temporally (i.e. in utero).

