where the parameters are as defined in Specific Aim 1. The  $k$  measured covariates for these analyses will be environmental, maternal, and child factors specific to 25(OH)D levels, such as sun exposure behavior, dietary intake of Vitamin D, and ethnicity. Additionally, any relevant covariates from Table 9 demonstrating main effects that have biologically plausible interactions with Vitamin D supplementation will be tested for effect modification. For both models, it is assumed that  $\varepsilon_i \sim N(0, \sigma^2)$ . The hypothesis that  $\delta_k=0$  will be used to examine whether any of these factors predict 25(OH)D levels, and the results will be used to adjust for any distributional imbalances of these factors across Vitamin D supplementation groups. As with the previous specific aims, we will also tests for effect modification via the hypothesis that  $\eta_k=0$ , or whether any maternal, child, or demographic/environmental covariates modify the relationship between vitamin D intake and circulating 25(OH)D levels in mother's plasma or cord blood. Additionally, we will follow the guidelines outlined in Specific Aim 2 to obtain the most parsimonious model.

The hypothesis that 25(OH)D levels in the child's blood will be higher in the 4400 IU group at birth, age 1 and age 3 will be tested using a repeated measures analysis framework such as generalized estimating equations.

#### P.2.d. Plan for Specific Aim 5

This specific aim investigates whether sufficient vitamin D supplementation in the pregnant mother is associated with reduced incidence of preterm birth (birth <37 weeks gestation) and/or preeclampsia, gestational hypertension, and/or HELLP syndrome compared to a usual care control group in VDAART.

The hypothesis that the incidence of preterm birth/preeclampsia, gestational hypertension and HELLP syndrome (PB/PE) is reduced in the high-dose vitamin D supplementation will be tested using logistic regression, allowing for fixed effect of center. Additional analysis will consider the modification of vitamin D exposure effects by maternal demographic/behavioral factors such as maternal age, BMI and weight gain during pregnancy, and maternal history of asthma/allergy, race, and other factors potentially associated with preterm birth/preeclampsia, gestational hypertension, HELLP or vitamin D exposure.

Letting  $M_i$  be an indicator function for the primary endpoint, PB/PE, for the  $i^{\text{th}}$  subject, the model is:

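### Treatment-by-covariate tests for Aims 1, 3 and 5 admit variables that arise after randomisation, so an interaction can appear without true effect modification

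*Supplement*

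**What the plan says.** The primary model in P.2.a (Plan for Specific Aim 1) contains treatment and centre. A second model adds covariates and their products with treatment, and the product coefficients are tested as effect modification. The text names modifiers "such as maternal age, BMI and weight gain during pregnancy, maternal history of asthma/allergy". It then narrows the candidates: "For example, only the prenatal and some delivery variables (e.g., gestational age, birthweight, length) listed in Table 3 will be considered". The reason given is that modifiers should act in utero.

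Table 3 lists gestational age and "Birthweight, length, head circumference" under delivery variables, so these are values at birth. Its prenatal block includes weight gain, medication use in pregnancy, and pregnancy complications with pre-eclampsia as an example.

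A covariate reaches interaction testing only if its main effect is significant and modification is biologically plausible. P.3 then applies an FDR correction for the number of models. Neither step asks when the covariate was measured, and the Addendum to the Analysis Plan leaves the list unchanged.

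For Aim 3, P.2.c adopts the same covariates. Its pointer is to Specific Aim 2, which was the asthma aim before Aims 1 and 2 were exchanged; I read it as P.2.a. The Aim 5 plan in P.2.d uses the same model and names "maternal age, BMI and weight gain during pregnancy, and maternal history of asthma/allergy, race". Of the variables at issue it names weight gain only.

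Section IV sets randomisation at 10-18 weeks. Aim 5 in Section II asks whether supplementation is "associated with reduced incidence of preterm birth (birth <37 weeks gestation), preeclampsia, gestational hypertension", among other complications.

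**The concern.** Randomisation makes the arms comparable within levels of anything fixed beforehand. It does not do so within levels of something that treatment may change. If vitamin D prevents some preterm births, the treated children who are still born preterm are a selected group and need not resemble the control children born preterm. A difference in asthma between them then mixes treatment effect with selection, and the product coefficient no longer measures effect modification.

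The protocol itself proposes such an effect for preterm birth and pre-eclampsia. For birthweight, length, weight gain and medication use an effect is plausible or possible, but is not stated as a hypothesis. The in utero rationale selects the treatment period, which is where the difficulty lies.

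In the Aim 5 plan, total weight gain has a further problem. It depends on how long the pregnancy lasts, and preterm birth is part of the outcome.

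At stake is a false statement that some children (for example preterm or small ones) are helped or harmed more than others.

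**Working it through.** The plan gives no figure for its interaction tests. For context, its power of 0.906 for 50% against 37.5% with 330 per arm does reproduce. With mean proportion 0.4375, z = [0.125·√330 − 1.96·√(2·0.4375·0.5625)] / √(0.5·0.5 + 0.375·0.625) = (2.271 − 1.375)/0.696 = 1.287, so power is 0.901.

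**Exact illustration: vitamin D has no effect on asthma in anyone.**

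- From Q.5: control rate 10%, halved to 5%. Q.5 gives this for a composite of pre-eclampsia and preterm labour; applying it to preterm birth alone is my assumption.
- Assumed, not in the documents: a shared cause carried by 25% of mothers, with preterm risk 20% in carriers and 6.7% in others, and asthma 60% and 40%.

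Control preterm births: 0.25·0.20 = 0.05 from carriers and 0.75·0.067 = 0.05 from others. Half are carriers, so asthma is 0.5·0.6 + 0.5·0.4 = 0.50. Overall asthma is 0.25·0.6 + 0.75·0.4 = 0.45 in both arms.

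Treated preterm births total 5% in every row below. Only the split of the prevention differs. For example, preventing 20% in carriers and 80% in others leaves 0.04 and 0.01, so 80% are carriers; asthma is 0.8·0.6 + 0.2·0.4 = 0.56 and the odds ratio is (0.56/0.44)/(0.50/0.50) = 1.27.

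| Prevented, carriers | Prevented, others | Asthma, treated preterm | OR preterm | OR term |
|---|---|---|---|---|
| 0% | 100% | 0.60 | 1.50 | 0.99 |
| 20% | 80% | 0.56 | 1.27 | 1.00 |
| 40% | 60% | 0.52 | 1.08 | 1.01 |
| 50% | 50% | 0.50 | 1.00 | 1.01 |
| 60% | 40% | 0.48 | 0.92 | 1.02 |
| 80% | 20% | 0.44 | 0.79 | 1.02 |
| 100% | 0% | 0.40 | 0.67 | 1.03 |

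With asthma 70% and 35%, the first two rows give 2.11 and 1.54 in preterm children.

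**How often the test of no interaction rejects at nominal 5%, 330 per arm, still with no effect on asthma.**

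- Scenario above, first two rows (4,000 simulated trials each): about 6-8% with asthma 60%/40%, about 9-20% with 70%/35%. With equal prevention it is 4-5%.
- Same rows, requiring also a significant main effect of preterm birth (p<0.05, my reading of the gate) and before FDR: about 1-2% and 4-10%.
- A second binary scenario (20% carriers, preterm risk 30% against 5%, outcome 80% against 40%): 11.1% when prevention is 90% in others and 10% in carriers, 7.5% for 80%/20%, 3.9% for equal prevention, 4.4% with no effect on preterm birth.
- A continuous, birthweight-like modifier whose low values treatment raises: 4.8% to 14.7%; with no effect on the modifier, 4.2% to 5.3%.

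At 3,300 per arm the second binary scenario gives 86.5% and 62.8% under unequal prevention and 5.1% under equal prevention. The continuous one gives 13% to 83%. A rate that climbs with sample size marks a bias, not chance.

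**The case against.** These are additional analyses, gated and FDR-adjusted. About 33 control children (0.10·330) and 17 treated children (0.05·330) would be preterm, so any interaction estimate would be very imprecise. After the gate, a declared false subgroup is unlikely except under harsh assumptions. The larger odds ratios need vitamin D to prevent 80-100% of preterm births in one risk group and 0-20% in the other, and nothing in the documents supports such selectivity. All of this stands and limits the size of the point. It does not restore the meaning of the coefficient: the gate asks whether a covariate predicts the outcome, which a shared cause ensures, and FDR addresses the number of tests.

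A reader might go further in four ways that the documents do not support.

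- That a more effective Aim 5 means more distortion. The table holds the reduction at 50% throughout, and the odds ratio runs from 0.67 to 1.50. What matters is how unequally prevention falls.
- That the Aim 5 plan also names gestational age at birth and birthweight as modifiers. It does not.
- That these tests are the plan's only word on who benefits. Section II.A of the Addendum plans analyses by baseline and follow-up maternal 25(OH)D, and the Aim 5 plan mentions stratified analyses with an acknowledged loss of power.
- That the primary result is at risk. The interaction terms are absent from that model.

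**Conclusion.** The point holds as a fault of specification with modest expected consequences. For gestational age at birth and pre-eclampsia, the protocol's own Aim 5 supplies the treatment effect on the modifier. For the other variables that effect is an assumption. A spurious interaction also needs a shared cause of modifier and outcome, with prevention falling unequally across it. If prevention is proportional the artefact is about nil. Under the unequal-prevention scenarios tried, the ungated rejection rate at 330 per arm is mostly about 6-15%, reaching about 20% at the harshest; a mild continuous case stays at 4.8%. The gate and FDR step lower the chance of a declared finding. The direction cannot be predicted. The shared-cause strengths and prevention splits are illustrative, so these rates show what can happen, not what is expected.

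**What to change.** In P.2.a, P.2.c and the Aim 5 part of P.2.d, state that treatment-by-covariate tests use only variables fixed before randomisation: for example maternal age, pre-pregnancy BMI, parental history of asthma or allergy, race/ethnicity and baseline 25(OH)D. Take gestational age at birth, birthweight, length, pregnancy weight gain, pregnancy complications and medication use in pregnancy off the modifier list. Report gestational age, birthweight, weight gain and complications by arm as treatment outcomes, or use them in an analysis labelled exploratory or mediation, with its assumptions stated. Correct the pointer in P.2.c at the same time.

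The cost is a change of wording. No new data are needed, and there are fewer interaction tests to correct for. The plan gives up formal tests of modification by birth variables, which could not have been read as effect modification in any case.

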#### **P.2.a.1. Interim Analyses for Specific Aim 1**

For the primary aim of asthma and/or recurrent wheeze, as well as the other specific aims, we have developed an interim analysis plan to monitor this composite endpoint over the course of the study. The interim analysis plan, for all four specific aims, is discussed in section VII.K.

#### **P.2.b. Plan for Specific Aim 2**

For this analysis, our N will be 800, since most of the dropouts will be expected to occur after delivery. Thus, the expected drop in N due to the 8% miscarriage rate was applied. We will test the hypothesis that the dose of 4,400 IU per day is sufficient to get 90% of the women to a sufficient level of 25(OH)D of at least 75 nmol/L, primarily using a logistic regression model, with randomization group (i.e. intervention group vs. usual care) as the independent variable. The dependent variable will be 25(OH)D level at delivery. We will adjust our analyses for other covariates that may affect 25(OH)D level, such as sun exposure (from the SmartProbe and the sun exposure questionnaire), age, and diet (calculated vitamin D intakes from dietary sources).

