**F. Measurement of 25(OH)D**

Blood will be drawn from the mothers at randomization, at the in-person research prenatal visit at 32-38 weeks gestation, and at 1 yr after delivery. Cord blood will also be collected at delivery. Blood from the child will be collected at 1 yr and at 3 yrs. All specimens will be shipped to the DCC, where they will be logged in and processed. Measurement of 25(OH)D will be performed at the Channing Laboratory DCC as previously described. Twenty five (25) microliters of serum or plasma (EDTA or Heparin) is required for the 25-OH-D extraction, however, 100 microliter samples will be aliquoted to allow for duplicate measurements on each sample. A chemiluminescence assay will be employed. The LIAISON® 25 OH Vitamin D assay (DiaSorin, Inc., Stillwater, MN) is a direct competitive chemiluminescence immunoassay (CLIA) for quantitative determination of total 25 OH vitamin D in serum or plasma. During the first incubation, 25 OH Vitamin D is dissociated from its binding protein and binds to the specific antibody on the solid phase. After 10 minutes the tracer, (vitamin D linked to an isoluminol derivative) is added. After a second 10 minute incubation, the unbound material is removed with a wash cycle. Subsequently, the starter reagents are added to initiate a flash chemiluminescent reaction. The light signal is measured by a photomultiplier as relative light units (RLU) and is inversely proportional to the concentration of 25 OH vitamin D present in calibrators, controls, or samples. In order to monitor assay performance each assay will include one quality control sample. The control will be treated as unknown specimen and multiple (5) determinations will be made. Assay variation will be determined and acceptable performance limits will be defined as ≤15 C.V. In addition 20% of the samples will also be re-measured in [name] laboratory in the Medical University of South Carolina.

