### P.3 Multiple comparisons.

All pre-specified hypotheses will be tested individually at the 0.05 level of significance, using a conservative two-sided alternative hypothesis (even when the stated hypothesis is one-sided). More specifically, the primary and secondary hypotheses of Vitamin D supplementation and Asthma/Recurrent Wheeze, Allergy/Eczema/LRI, will not be adjusted for multiple comparisons, since they have been defined a priori and are limited in scope. Additionally, an interim analysis plan has been developed for the primary outcome to adjust for the number of times (3) asthma and/or recurrent wheeze will be analyzed over the study period. Since 25(OH)D status is being examined in 5 separate analyses (maternal plasma at 26-28 weeks, maternal plasma at delivery, cord blood at delivery, infant plasma at years 1 and 3), this analysis will be adjusted for 5 multiple comparisons (i.e., using Bonferroni correction). Finally, any findings with respect to interaction terms (i.e., exploring whether environmental and demographic covariates affect the relationship between Vitamin D supplementation and the outcome of interest) for any of the hypotheses will be adjusted (i.e., using FDR methodology) for the number of models tested, and interaction testing will be limited to those defined in sections D.14.2a-c, in order to limit the potential for spurious findings. Any serendipitous findings coming from exploratory analyses will be clearly reported as such, and test statistic p-values will be adjusted by the number of exploratory hypotheses considered (using FDR or another appropriate procedure for multiple comparisons adjustment).

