**Table 6. Power to detect a 25-35% reduction in secondary outcomes for 870 subjects in a multi-site study, (effectively 660 patients, assuming an 8% miscarriage rate and 18% loss to follow-up)**

| Mean Incidence of secondary outcome in 400 IU group | Percent reduction in secondary outcome in 4400 IU group |            |            |
|------------------------------------------------------------|----------------------------------------------------------------|------------|------------|
|                                                            | 35%                                                     | 30% | 25% |
| 0.50                                                | 0.998                                                          | 0.982      | 0.913      |
| 0.45                                                | 0.992                                                          | 0.958      | 0.858      |
| 0.40                                                | 0.973                                                          | 0.906      | 0.779      |
| 0.35                                                | 0.936                                                          | 0.845      | 0.691      |
| 0.30                                                | 0.890                                                          | 0.736      | 0.608      |
| 0.25                                                | 0.795                                                          | 0.654      | 0.531      |

**Q.4. Power for Specific Aim 4.** The research to date on the impact of vitamin D supplementation on 25(OH)D is presented in Table 1. As noted in the table, only 4 studies have been conducted on pregnant women, all had fewer than 100 subjects, and the maximum daily dose for these studies was 1,600 IU. The only data available on 25(OH)D status in the supplementation ranges we are proposing has been provided by [name] (unpublished data, see section III). In a study of 347 pregnant women (African Americans, Hispanic,

and Caucasians) on either 4000 IU (supplemented) or 400 IU (control) of Vitamin D daily, the maternal plasma 25(OH) D levels were 115 nmol/L in supplemented subjects, and 80 nmol/L in controls after 8 months of supplementation, an overall difference of 35 nmol/L. The estimated standard deviation for 25(OH)D levels in these ranges is 40.

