For maximum flexibility in the analysis, we will use a Lan-Demets alpha spending function with O'Brien-Fleming bounds. The software program LANDEM (<http://www.biostat.wisc.edu/landemets/>) was used to calculate the crossing boundaries, which, for the first and third specific aims are  $|z|=4.3329$ ,  $2.9631$ ,  $2.3590$ , and  $2.0141$ , at the first, second, third and final analyses, respectively. For the second and fourth specific aim, with 3 looks in total, the crossing boundaries are  $|z|=3.7103$ ,  $2.5114$ , and  $1.993$  at the first, second looks and final analysis, respectively. While the looks in the interim analyses have been predetermined, the Lan-DeMets procedure provides a spending function approach which does not require pre-specification of the frequency or timing of interim looks. This can be advantageous if the timing of data collection varies or if the need for more frequent monitoring arises. Conservative O'Brien-Fleming bounds are used to preserve most of the type-I error for the final analysis. For all specific aims, the hypothesis tests are conducted with two-sided alternatives (i.e. a two-sided p-value). If the boundaries are crossed for efficacy endpoints at any interim analyses, for any of the aims, the study will continue. If the boundaries are crossed in Specific Aims 2-4, the primary specific aim, whether Vitamin D supplementation in pregnancy is associated with a reduction in asthma and/or recurrent wheeze risk, still needs to be assessed, thus the study should continue to monitor this endpoint. If the boundaries are crossed during an interim analysis of the primary aim, the study will also be continued, as the target intervention period (i.e., pregnancy) will have passed for all recruited subjects, and will feel that it is most important to examine the impact of this intervention on the children at 3 years of age. If the study is stopped early due to the success of the intervention, important clinical and outcome information may be lost. Therefore, we feel that it is important to continue the study even if interim analysis boundaries are crossed. The only situation when consideration will be given to prematurely stopping the trial will be for safety considerations. It is inevitable that adverse health events will be observed in all contexts noted above even if both treatments have no biological effects whatsoever. If the rate of adverse events on the active arm substantially and persistently exceeds the rate on the control arm, even in the absence of biological theory that connects the adverse events to vitamin D exposures, and no evidence of therapeutic effect or benefit of the active treatment is apparent in interim analyses, then premature termination of the study may be considered on safety grounds. The DSMB will be asked to articulate

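### Aim 2 states a 90% hypothesis that its between-arm test does not address, the 25(OH)D analyses rely on maternal samples the schedule does not contain, and Aim 4's stated alpha and boundaries disagree

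*Supplement*

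**What the plan says.** All references are to the Current Protocol unless stated.

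- **Aim.** Section II lists Aim 2 as a primary aim, in comparative terms: "To determine whether a vitamin D dose of 4,400 IU per day vs. the standard 400 IU/day in pregnancy is sufficient" to keep mothers at or above 75 nmol/L. It gives no 90% figure.
- **Hypothesis and test.** P.2.b turns this into the hypothesis that "the dose of 4,400 IU per day is sufficient to get 90% of the women to a sufficient level of 25(OH)D". The test is a logistic regression "with randomization group (i.e. intervention group vs. usual care) as the independent variable". On the outcome it says: "The dependent variable will be 25(OH)D level at delivery".
- **Power.** Q.2 and Table 5 give power for the difference between arms, 400 women each, with 70%, 80% or 90% above 75 nmol/L on 4,400 IU against 30%, 40% or 50% in controls. All nine cells read above 0.999.
- **Sampling.** After the draw at randomisation, VI.F takes maternal blood "at the in-person research prenatal visit at 32-38 weeks gestation, and at 1 yr after delivery". Table 2, the follow-up paragraph of Section V and Sources of Research Material in Section VIII agree, and show only cord blood at delivery.
- **Test family.** P.3 applies a Bonferroni correction over five 25(OH)D analyses: "maternal plasma at 26-28 weeks, maternal plasma at delivery, cord blood at delivery, infant plasma at years 1 and 3". Q.4 accordingly uses 0.01 per test, then says that Aim 4 follows the same interim procedure as Aim 2.
- **Boundaries.** VII.K: "For the second and fourth specific aim, with 3 looks in total, the crossing boundaries are" 3.7103, 2.5114 and 1.993 in absolute z.

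**The concern.** The hypothesis concerns one proportion in one arm. The null of the model is equal odds in two arms. P.2.b, Q.2, P.3, VII.K and the Addendum to the Analysis Plan contain no rule for judging whether 90% was reached, so the hypothesis goes untested whatever the data show.

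The outcome is also attached to a sample that the schedule does not contain. P.2.d and VII.K rely on maternal blood at delivery too, and P.3 and Q.4 add a maternal sample at 26-28 weeks. Followed literally, the analyst has no scheduled specimen for Aim 2 or for two of the five corrected tests.

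Lastly, the error rate for Aim 4 depends on whether one follows the 0.01 or the boundaries.

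**Working it through.** **1. Reproducing Table 5.** Inputs: n = 400 per arm (870 × 0.92 = 800), final boundary 1.993, hardest cell 50% against 70%, pooled proportion 0.60.

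(0.20 × √400 − 1.993 × √(2 × 0.60 × 0.40)) / √(0.50 × 0.50 + 0.70 × 0.30) = (4.000 − 1.381) / 0.678 = 3.86, so power = 0.99994.

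A Wald test on the log odds ratio gives 0.9999 as well, and the other eight cells round to 1.000. Table 5 is right for the question it asks.

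**2. What that test says about 90%.** In the same cell the expected count on 4,400 IU is 280 of 400, with an exact 95% interval of 65.2% to 74.5%. The test is almost certainly significant, and 90% is far outside the interval. Against 50% in controls, a true 60% on 4,400 IU already gives about 80% power.

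**3. A test that would address 90%.** The protocol plans none, so this is an assumption: exact binomial, 4,400 IU arm only, null of at most 90%, one-sided 0.025, n = 400. The smallest count that rejects is 372 (93.0%). At 372 the exact 95% lower limit is 90.04%; at 371 it is 89.8%.

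| True proportion | Chance of at least 372/400 |
|---|---|
| 88% | 0.0007 |
| 90% | 0.023 |
| 92% | 0.26 |
| 93% | 0.55 |
| 95% | 0.97 |

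**4. Where the true proportion may lie.** Q.4 reports that "the maternal plasma 25(OH) D levels were 115 nmol/L in supplemented subjects, and 80 nmol/L in controls", with SD 40. If levels are normal, P(≥75) = Φ((115 − 75)/40) = Φ(1.00) = 84% on supplementation and Φ((80 − 75)/40) = Φ(0.125) = 55% in controls. A log-normal shape gives 86% for the supplemented group. Table 1 has two other groups at 4,000 IU: 111 ± 28.5 (lactating women) and 96 ± 15 (healthy adults). These imply Φ(1.26) = 90% and Φ(1.40) = 92%. Section III says nearly all women on 4,400 IU reached 75 nmol/L. So the documents' figures run from 84% to nearly all.

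**5. Maternal samples, side by side.**

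| Maternal time point | Scheduled in VI.F and Table 2 | Used in the analysis text |
|---|---|---|
| Enrolment | yes | – |
| 26-28 weeks | no | P.3, Q.4 |
| 32-38 weeks | yes | not named |
| Delivery | no (cord blood only) | P.2.b, P.2.d, P.3, Q.4, VII.K |
| 1 year | yes | – |

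**6. Alpha.** Recomputing Lan-DeMets boundaries of O'Brien-Fleming type for three equally spaced looks:

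| Two-sided alpha | Look 1 | Look 2 | Final |
|---|---|---|---|
| 0.05 | 3.7103 | 2.5114 | 1.993 |
| 0.0125 | 4.59 | 3.15 | 2.51 |
| 0.01 | 4.72 | 3.25 | 2.59 |

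The printed boundaries are therefore the 0.05 set. VII.K ties them to the delivery outcomes, maternal and cord blood. Two independent tests at 0.05 give 1 − 0.95² = 9.75%; at 0.01 they give 1 − 0.99² = 2.0%.

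**The case against.** The strongest reply is that Aim 2 in Section II is comparative, Table 5 powers a comparison and the model is a comparison, so a single sentence in P.2.b is out of line. That stands, and it settles the repair: the sentence should move to the test. The fitted model could also yield an estimated proportion for the 4,400 IU arm, but no criterion for judging it is given.

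Four stronger readings are tempting and are not supported.

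- *The trial would declare 90% confirmed from the between-arm p-value.* No passage states such a success rule.
- *The treated arm will fall short of 90%.* The 84% rests on an assumed normal shape and an SD given for the Aim 4 power calculation. Section III and Table 1 point higher.
- *Maternal blood at delivery is certainly not collected.* VII.A still describes collecting it in labour and delivery, and Protection against Risks in Section VIII still mentions a maternal draw at delivery. The change summary (item 9b) records its removal, so these are probably leftovers, but the current text contradicts itself.
- *Family-wise error is 23%.* That is 1 − 0.95⁵, which needs five independent tests all at 0.05. VII.K puts the last of these looks at year 4 month 5, while the timeline in VII.L starts the 3-year visits in year 5 month 5, so this boundary cannot govern all five. Positive correlation between maternal and cord levels would usually lower even the 10%.

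On weight, P.1 lists maternal 25(OH)D among the secondary outcomes and VII.K treats asthma and wheeze as the primary aim. Nothing here touches the asthma/wheeze analysis.

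**Conclusion.** The point holds as a mismatch of hypothesis, test, sample and alpha within the 25(OH)D analyses. The 90% hypothesis in P.2.b is left untested by its named model, whose power is above 0.999 even at 70% against 50%. The arithmetic in Table 5 is sound.

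The maternal time points in the analysis text conflict with the sampling schedule, and the remaining references to maternal blood at delivery must be reconciled with it.

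For Aim 4, the 0.01 in Q.4 and the 0.05 boundaries in VII.K cannot both apply. The consequence is about 10% against about 2% error for the two delivery outcomes, assuming independence.

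The one-sample figures assume 400 evaluable women on 4,400 IU. With 330, the rule needs 308, and power is 0.46 at a true 93% and 0.93 at 95%.

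**What to change.** 1. **P.2.b.** Define the Aim 2 outcome as 25(OH)D at or above 75 nmol/L (yes/no) at the scheduled 32-38 week maternal sample. Keep the randomised between-arm comparison as the test of Aim 2, and reword the hypothesis as a difference between arms.
2. **The 90% statement.** Report the proportion in the 4,400 IU arm with an exact 95% confidence interval. Claim that at least 90% reach the target only if the lower limit is at least 90% (372 of 400), and state the power: 0.55 at a true 93%, 0.97 at 95%, 0.02 at exactly 90%.
3. **Time points.** Replace the unscheduled maternal samples in P.2.d, P.3, Q.4 and VII.K with the 32-38 week sample, and reconcile VII.A and Protection against Risks in Section VIII with VI.F and Table 2.
4. **Number of tests.** Restate the 25(OH)D family. P.2.d analyses the child levels at birth, 1 and 3 years in one repeated-measures model and also tests cord blood separately, so the count of five needs to be rederived. Say whether Aim 2 lies inside or outside this family.
5. **Boundaries.** Recompute the Aim 4 boundaries in VII.K at the resulting per-test alpha. For example, four tests at 0.0125 would give 4.59, 3.15 and 2.51.

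Cost: wording and a boundary calculation, with no sample beyond those already scheduled. The 90% claim becomes hard to support: if exactly 90% of women reach the target, it would be made about 2% of the time. The Aim 4 thresholds become stricter.
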